#### Physical and exercise assessment

The physiotherapists assess the handgrip strength and short physical performance battery (SPPB) score according to the study protocol. The medical doctor, physiotherapist or nurse administers the lifestyle questionnaire in an interview and educates the participant about lifestyle measures needed to ensure their safety and to maintain the prescribed amount of physical activity. The lifestyle questionnaire includes information about the family structure, occupational status, the amount of physical activity on a usual day, routine habits and housework, participation in sports or exercise, frequency of going out, and experiences of falls. Physical activity is measured using an accelerometer (Lifecorder®, Suzuken Co. LTD., Nagoya, Japan) at the protocol-defined assessment intervals. The QOL assessments are performed at T1 and T4 using the EORTC-QLQ-C30 questionnaire.

#### Nutritional assessment

At every assessment point, body weight (kg) is measured to the nearest 0.1 kg. The registered nutritionist assesses the nutritional status using the full version of the Mini Nutritional Assessment (full MNA®) and estimated ingested nutritional quantity using a 24-h recall method.

Lumbar skeletal muscle mass is measured at T1 and T4 by analyzing electronically stored CT images using the Slice-O-matic software (version 5.0, Tomovision, Montreal, Quebec, Canada) as previously reported [23].

#### Exercise and lifestyle interventions

The exercise and lifestyle interventions consist of a home-based muscle training program and physical activity program, respectively. Muscle training programs include three or five of the following five exercises: sit-to-stand, calf raise, knee extension, knee raise, and side-leg-raise with or without ankle weight (Fig. 2). One set includes 10 repetitions of each exercise. Patients perform 3 sets in a standard regimen, although that amount can be reduced based on the assessment made by the physiotherapists. Patients perform each exercise at the prescribed level three times a day at home. At T1, the physiotherapist educates the patients about level 2 of the muscle training program based on the standardized exercise education manual (Additional file 1: Appendix 1A). Physiotherapists choose the optimal level that will be followed by the patient until the next assessment according to the modified Borg scale (Additional file 1: Appendix 1B, C). Physiotherapists repeat this evaluation at each assessment point and prescribe the optimal exercise level that is to be followed until the next assessment (Additional file 1: Appendix 1D). At T4, physiotherapists prescribe the optimal exercise level that should be adhered to during the follow-up period. The physical activity program consists of lifestyle consultations and prescribed targets to encourage the patients to engage in the activities daily. The instructors in this program can be any medical staff member who understands the standardized manual (cf. medical doctor, nurses, physiotherapists, or occupational therapists). At T1, the instructor evaluates and discusses with participants the effectiveness of maintaining daily activities based on the results of the lifestyle questionnaire. If there are any issues that precludes the patient from safely implementing the lifestyle interventions, the instructor provides the participant with modifications to make the lifestyle interventions safer. The instructor prescribes individual targets for the next period according to the averages obtained previously (Additional file 1: Appendix 1E). At T4, the instructor prescribes the optimal target for the follow-up period.

**Fig. 2 Fig2:**
[figure not shown]
The detail of exercise program

#### Nutritional interventions

The nutrition intervention is mainly administered by registered nutritionists who understand the standardized manual for the NEXTAC-TWO study. The registered nutritionists assess the nutritional intake and status of the participants based on the full MNA® and estimate the ingested nutritional quantity using a 24-h recall method. They counsel the patients on how to improve their nutritional status of participants and prescribe supplements rich in branched-chain amino acids (Inner Power®, Otsuka Pharma Co., Ltd., Tokyo, Japan) for 12 weeks.

### Study objectives

The primary endpoint and secondary endpoints are listed in Table 3. The primary endpoint of this study is the disability-free survival. This endpoint is defined as the period from random assignment to the date of patients being evaluated as needing care based on the modified Katz index or death due to any cause. Overall survival is defined as the period from random assignment to the date of death due to any cause. Lean body mass (LBM) is one of the secondary endpoints. We use the lumber skeletal muscle mass index to analyze electronically stored CT images to estimate the LBM.

**Table 3 Tab3:** Endpoints for the trial

Primary endpoint	
The disability-free survival	
Secondary endpoint	
1) Lean body mass assessed by CT	
2) Physical function assessed by the hand-grip strength, SPPB score and physical activity measured by accelerometer	
3) Nutritional status assessed by body weight, MNA score and ingested nutritional quantity	
4) Quality of Life assessed by EORTC-QLQ-C30	
5) The proportion of patients treated with subsequent chemotherapy	
6) Overall survival, Progression free survival	
7) The cumulative number of days of hospitalization	
8) Activity of daily life	
9) Safety	

*CT* computed tomography, *SPPB* short physical performance battery, *MNA* Mini Nutritional Assessment, *EORTC-QLQ* The European Organization for Research and Treatment of Cancer Quality-of Life Questionnaire

### Data collection and monitoring

All data related to this study is collected through the electric data capturing system within 2 weeks of each planned visit. The data center at the clinical trial management unit of Shizuoka Cancer Center, Japan, is in charge for quality control of study data. Data managers will monitor an allowance of data entry and check range for data values. The role of data monitoring committee (DMC) is to review efficacy and toxicity of study intervention independently from the investigators. The DMC review reports of severe adverse events from researchers, monitoring reports from the data center, and analysis reports from biostatisticians. The DMC comprised from three medical doctors who are independent from the study and have no conflict of interest associated with this study. No regular auditing is planned.

### Statistical considerations

We set the recruitment period to 3 years, starting in August 2017. All participants who pass the screening are randomly assigned to the intervention group or the control group at a ratio of 1:1 in every stratified group, and they are followed for 2 years after randomization. The levels of stratification factors are as follows: (1) NSCLC or pancreatic cancer, (2) PS = 0/1 or PS = 2, and (3) cytotoxic chemotherapy or not.

With 64 patients per group, the trial achieves 80% power to detect an improvement in median disability-free survival from 8 months in the control group to 12 months in the intervention group using a two-sided log-rank test with a significance level of 0.20. Because we observed only a few dropouts from the NEXTAC program in the phase I study, we estimated the needed sample size with a small number of additional patients included. In total, 130 patients will eventually be included in the study. The disability-free survival and overall survival are estimated using the Kaplan-Meier method. To compare categorical variables, chi-square or Fisher’s exact tests are used. Continuous measures are compared using the Wilcoxon rank-sum test. For the primary endpoint analyses, *p*-values < 0.05 are considered significant.

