**Methods:**

Patients with chemo-naïve advanced non-small cell lung cancer or pancreatic cancer, age ≥ 70 years, performance status ≤2, with adequate organ function and without disability according to the modified Katz index will be eligible. In total, 130 participants will be recruited from 15 Japanese institutions and will be randomized into either the intervention group or a control group. Computer-generated random numbers are allocated to each participant. Stratification factors include performance status (0 to 1 vs. 2), site of primary cancer (lung vs. pancreas), stage (III vs. IV), and type of chemotherapy (cytotoxic vs. others). Interventions and assessment will be performed 4 times every 4 ± 2 weeks from the date of randomization. Interventions will consist of nutritional counseling, nutritional supplements (rich in branched-chain amino acids), and a home-based exercise program. The exercise program will include low-intensity daily muscle training and lifestyle education to promote physical activity. The primary endpoint is disability-free survival. It is defined as the period from the date of randomization to the date of developing disability or death due to any cause. This trial also plans to evaluate the improvements in nutritional status, physical condition, quality of life, activities of daily living, overall survival, and safety as secondary endpoints. Enrollment began in August 2017. The study results will demonstrate the efficacy of multimodal interventions for elderly cancer patients and their application for the maintenance of physical and nutritional conditions in patients with cancer cachexia. This work is supported by a grant-in-aid from the Japan Agency for Medical Research and Development.

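### The primary endpoint has two significance levels: the trial is sized for 80% power at two-sided 0.20, but judged at p < 0.05, where power would be only about 54–60%

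*Protocol article*

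**What the plan says.** Both levels stand in the protocol article under Statistical considerations.

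- **Sizing.** The test behind the sample size is specified as "using a two-sided log-rank test with a significance level of 0.20". On that basis 64 patients per arm are said to give 80% power, the target effect being a rise in the median of the primary endpoint from 8 to 12 months. The total is then rounded up for dropout: "In total, 130 patients will eventually be included in the study".
- **Decision rule.** The section's last sentence, which is expressly about the primary endpoint, sets a different threshold for the p-value: "values < 0.05 are considered significant". It does not say whether this p-value is one- or two-sided.

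Study objectives and Table 3 list one primary endpoint, disability-free survival, so both statements concern the same comparison. The article nowhere assigns 0.20 and 0.05 to different purposes. It gives no target number of events.

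**The concern.** A power figure belongs to a particular test at a particular level. Here it is quoted for one level, and the threshold for success is set at another. A result favouring the intervention with a two-sided p-value between 0.05 and 0.20 would be positive by the sizing rule and negative by the last sentence. The text does not say which conclusion the trial would draw, and the choice could be made once the p-value is known.

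The two rules also carry different risks. At 0.20 the false-positive rate is that of a screening trial. At 0.05 the chance of missing the effect the trial was designed to find is far above the 20% that a reader would take from the stated power.

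**Working it through.** **Inputs from Statistical considerations:** 64 per group (128 in all), 1:1 allocation, medians 8 and 12 months, two-sided 0.20 for sizing, p < 0.05 for the decision, 3 years' recruitment, follow-up of 2 years after randomization.

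**Assumptions, not in the article:** exponential survival, uniform accrual, no loss to follow-up. The follow-up statement can be read as exactly 24 months per patient, or as 36 months' accrual followed by 24 more months for everyone. Both readings are carried through.

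**Effect size.** HR = 8/12 = 0.667; |ln HR| = 0.4055.

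**Expected events.**
- Fixed 24 months: event probabilities are 1 − 2^(−24/8) = 0.875 (control) and 1 − 2^(−24/12) = 0.75 (intervention). Events = 64 × (0.875 + 0.75) = 104.
- 36 months' accrual (A) plus 24 months (F): event probability = 1 − [exp(−λF) − exp(−λ(A+F))]/(λA), with λ = ln 2/median. This gives 0.962 and 0.895, mean 0.928. Events = 128 × 0.928 = 118.8.

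**Power (Schoenfeld)** = Φ(|ln HR| × √events / 2 − z). The first term is 0.4055 × √104 / 2 = 2.068 for 104 events and 0.4055 × √118.8 / 2 = 2.210 for 118.8 events.

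| Level | z | 104 events | 118.8 events |
|---|---|---|---|
| Two-sided 0.20 | 1.282 | Φ(0.786) = 78.4% | Φ(0.928) = 82.3% |
| Two-sided 0.05 | 1.960 | Φ(0.108) = 54.3% | Φ(0.250) = 59.9% |
| One-sided 0.05 | 1.645 | Φ(0.423) = 66.4% | Φ(0.565) = 71.4% |

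**The article's own figure.** The stated 80% lies between 78.4% and 82.3%, so it reproduces at two-sided 0.20. One-sided 0.20 would give 89–91%, which does not match. The level in the sizing sentence is therefore not a misprint.

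**Checks.**
- A simulated log-rank test (20,000 runs, 64 per group) gives 78.6% and 82.6% at two-sided 0.20, and 54.5% and 59.5% at two-sided 0.05.
- Freedman's formula gives 53.2% and 58.7% at two-sided 0.05.
- With all 130 patients, Schoenfeld gives 54.9% and 60.5% at two-sided 0.05.
- If all 128 patients had an event, power at two-sided 0.05 would still be only 63%.

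**Events needed for 80% power** = 4(z_α + z_β)²/(ln HR)²:
- Two-sided 0.20: 4 × (1.282 + 0.842)²/0.4055² ≈ 110.
- Two-sided 0.05: 4 × (1.960 + 0.842)²/0.4055² ≈ 191. This means 103 per group (36 + 24 months) or 118 per group (fixed 24 months), so 206 or 236 patients. Freedman's 197 events raises the upper figure to 122 per group, or 244.

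**HR detectable with 80% power at two-sided 0.05** = exp(−2 × 2.802/√events): 0.58 with 104 events, 0.60 with 118.8.

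**Zone where the rules disagree (104 events, favouring the intervention).** The critical HR is exp(−2z/√104): 0.78 at two-sided 0.20 and 0.68 at two-sided 0.05. The probability of landing between them is 78.4% − 54.3% = 24% if the design effect is true. Under no effect it is (0.20 − 0.05)/2 = 7.5%.

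**The case against.** The strongest reply is that the power statement is correct as written. The article ties 80% to two-sided 0.20, and at that level it reproduces. A relaxed level is an accepted choice in a randomized phase II trial, and the 0.05 sentence may be a conventional line carried over by mistake. This stands as far as it goes. A reader might infer that the stated power is false and that the true figure is 54–60%. The documents do not support that: the lower range applies only if the 0.05 sentence governs, and nothing shows which level was intended.

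The sidedness of the 0.05 rule is also unstated. Read as one-sided, it gives about 66–71%, still short of 80%. The upper figure of 60% depends on the longer follow-up reading; the more literal fixed 24 months gives 54%.

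A reader might also cite the abstract's statement that "The study results will demonstrate the efficacy of multimodal interventions for elderly cancer patients" as a sign that 0.05 was meant. It is forward-looking wording about the aim and says nothing about the significance level, so the point does not rest on it.

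Another tempting figure is a 15% null probability for the zone of disagreement. That counts both directions; half of it lies where the intervention looks harmful and could not be called a success.

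Finally, a statistical analysis plan not shown here may settle the level, and an article condenses its protocol. But this is not an omission. The article states both levels for one endpoint, and a single level elsewhere would still leave this text to be corrected.

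**Conclusion.** The point holds as an unreconciled contradiction, wrong as written: one primary comparison, two significance levels, and a power figure that belongs to only one of them. If two-sided 0.20 governs, the 80% stands and the last sentence is wrong. If two-sided 0.05 governs, the planned sample has about 54–60% power, so the design effect would be missed 40–46% of the time rather than 20%. In the first case the sizing is sound; in the second it is not. On the 104-event reading, and if the design effect is true, the conclusion would depend on the choice of rule in about one trial in four. These sizes rest on exponential survival, uniform accrual and no loss to follow-up, because the article states no event count. The contradiction itself rests on no assumption.

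**What to change.** State one level for the primary comparison before the primary analysis is run. (No blinding is described, so unblinding is not a usable milestone.) Two routes need no additional patients:

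- **(a) Keep the sizing level.** Replace the p < 0.05 sentence with a two-sided log-rank test at 0.20, as sized, and say that a positive result is a phase II signal that needs confirmation. The cost is a weaker claim.
- **(b) Keep 0.05.** State that it is two-sided, and restate the power as about 54–60% for 8 versus 12 months, with a hazard ratio of about 0.58–0.60 detectable at 80% power. The cost is a less favourable stated power, knowingly accepted.

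Restoring 80% power at two-sided 0.05 would instead mean resizing to about 206–244 patients, against the 130 planned. Either (a) or (b) changes one sentence. Any separate statistical analysis plan should carry the same level.

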## Methods

### Study design and participants

The NEXTAC-TWO study is a multicenter, randomized phase II study with 130 participants allocated 1:1 to an intervention group or a control group. One hundred thirty patients will be recruited from 15 Japanese institutions according to the inclusion criteria and exclusion criteria listed in Table 1. Participating institutions include public hospitals, university hospitals, and cancer centers in Japan. The list of study institutions is available in Additional file 2. Recruitment began in August 2017 and is expected to be completed in July 2020.

**Table 1 Tab1:** Inclusion and exclusion criteria

Inclusion Criteria	
1) Diagnosis of advanced non-small cell lung cancer or inoperable pancreatic cancer	
2) Scheduled for systemic cancer therapy (i.e. chemotherapy, and/or targeted therapy and/or immunotherapy)	
i. In pancreatic cancer patients, planned systemic chemotherapy only allows of the combination of gemcitabine with nanoparticle paclitaxel.	
3) Eastern Cooperative Oncology Group (ECOG) performance status 0 to 2	
4) Age ≥ 70 years	
5) Body weight of 6 month ago can be confirmed	
6) An expected survival of ≥3 months as judged by investigators	
7) Written informed consent	
8) Adequate organ function	
i. Hemoglobin ≥8.0 g/dl	
ii. Total bilirubin ≤2.0 mg/dl	
iii. Aspartate aminotransferase ≤150 IU/L	
iv. Alanine aminotransferase ≤150 IU/L	
v. Serum creatinine ≤2.0 mg/dl	
vi. Arterial oxygen saturation (SpO_2_) ≥ 90% or partial pressure of oxygen in arterial blood (PaO_2_) ≥ 60 Torr in room air	
vii. Resting heart rate < 120 beat per minute	
Exclusion criteria	
1) Patients received prior chemotherapy except adjuvant chemotherapy	
2) Active malignancy requiring cancer treatment including chemotherapy, radiotherapy and surgery within 3 months	
3) Patients who need nursing care at following situation (based on Katz Index)	
i. Bathing	
ii. Dressing	
iii. Transferring	
iv. Feeding	
4) Symptomatic brain metastasis or leptomeningeal carcinoma	
5) Bone metastasis with high risk of fracture	
6) Patients who are difficult to evaluate or intervene with cardiovascular disease, bone and joint disease, neuromuscular disease etc.	
7) Patients who are difficult to participant due to psychiatric disorder	
8) Patients who are difficult to oral intake	

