9) History of acute myocardial infarction, unstable angina, uncontrollable hypertension, and symptomatic sustained arrhythmia within 6 months. Stable atrial fibrillation treated with appropriate anticoagulation therapy is allowed.	
10) Uncontrollable diabetes mellitus	
11) Patients whose appropriate period has not passed since prior treatment	
i. Surgery: 7 days	
ii. Palliative radiation: 1 day	
iii. Minor surgery (i.e. biopsy): 1 day	
12) Screening failure	
i. Patients who failed to wear the accelerometer for more than 4 days	
ii. Patients who could not properly handle the accelerometer	
iii. Patients who failed to initiate first-line therapy within 14 days of enrollment	

This study consisted of two periods, namely, the screening period and the study period (Fig. 1). In the screening period, after written informed consent is obtained, the investigator educates the eligible patients regarding the wearing and handling of an accelerometer. Patients who demonstrated their ability to wear and handle the accelerometer for at least 4 days are enrolled and randomized. If the patients cannot wear the accelerometer or the investigator determines that the patient is not able to handle the accelerometer adequately, the patient is judged to be ineligible and is not enrolled in the study. The study period is defined as the time between the date of study enrollment and the date of the occurring disability event or death.

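### The only test named for disability-free survival uses no covariate, although a pre-randomisation activity value should exist for nearly every patient; power may be lost if that value is prognostic

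*Protocol article*

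**What the plan says.** Under Statistical considerations, the power statement reads "With 64 patients per group, the trial achieves 80% power" for an improvement in the median "from 8 months in the control group to 12 months in the intervention group", "using a two-sided log-rank test with a significance level of 0.20". For disability-free survival the same section adds only Kaplan-Meier estimation and the criterion that p-"values < 0.05 are considered significant". It mentions no covariate, no Cox model and no stratified test. It does not call the log-rank test unadjusted either, and it does not rule out adjustment.

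Under Study design and participants, the screening period ends with this rule: "Patients who demonstrated their ability to wear and handle the accelerometer for at least 4 days are enrolled and randomized". Non-wearers count as screening failures. Table 2 schedules a physical activity measurement at T1 in both arms, and Table 3 lists accelerometer activity among the secondary endpoints. For the intervention arm, the section on exercise and lifestyle interventions says: "The instructor prescribes individual targets for the next period according to the averages obtained previously".

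**The concern.** A daily activity value obtained before allocation is objective, should be almost complete, and is a natural candidate predictor of an endpoint built on loss of self-care or death. If it is prognostic and left out, two things follow.

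- In time-to-event data, frailer patients leave the risk set first. The marginal hazard ratio then drifts towards 1 over time, and the log-rank test loses power against the same pair of medians.
- Chance imbalance between the arms goes uncorrected. With 64 per group, the SD of the difference in mean baseline activity is √(2/64) = 0.18 SD.

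The planned power leaves little room for such losses.

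**Working it through.** **Inputs.** From Statistical considerations: medians 8 and 12 months, 64 per group (128 in total), two-sided 0.20, 3 years of recruitment, 2 years of follow-up after randomisation. Allocation is 1:1 (Study design and participants). The prognostic strength of baseline activity appears nowhere in the document, so it is varied.

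**Step 1: the plan's own figure.** With exponential survival, HR = 8/12 = 0.667 and ln HR = −0.405.

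- Events needed (Schoenfeld): 4(1.282 + 0.842)²/0.405² = 110.
- Each patient followed for 24 months, as worded: event probabilities 1 − 2^(−24/8) = 0.875 and 1 − 2^(−24/12) = 0.750, mean 0.8125. Expected events are 128 × 0.8125 = 104. Power = Φ(√104 × 0.405/2 − 1.282) = 78.4%.
- Uniform accrual over 36 months plus 24 months for all: event probabilities 0.962 and 0.895, 118.8 events, power 82.3%.

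The stated 80% lies between these two readings, so it reproduces.

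**Step 2: what adjustment would change.** The simulation used 10,000 trials per setting, 64 per group, and one standard-normal baseline covariate independent of treatment. The baseline hazard was solved so that the control median is 8 months after averaging over the covariate. The conditional treatment HR was 0.667. Because each patient's time is exponential, this stretches times by 1.5, so the intervention median is 12 months in every setting. The log-rank test was compared with the Wald test from a Cox model with treatment and the covariate. Monte Carlo error is about 0.4 points per entry.

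Power at two-sided 0.20, log-rank → adjusted Cox:

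| HR per SD (assumed) | 24 months per patient | 36 + 24 months |
|---|---|---|
| 1.0 | 77.9% → 77.7% | 82.4% → 82.2% |
| 1.2 | 76.7% → 78.1% | 79.7% → 80.8% |
| 1.35 | 74.8% → 77.9% | 78.0% → 81.8% |
| 1.5 | 72.3% → 77.4% | 75.6% → 81.4% |
| 2.0 | 63.0% → 76.3% | 65.0% → 79.4% |

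Adjustment does not lift power above the planning figure. It recovers most of what heterogeneity takes away.

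**Step 3: validity.** With no treatment effect and 24 months per patient, rejection rates at 0.20 were 0.201 (log-rank) and 0.202 (Cox) at HR per SD 1.0, and 0.197 and 0.199 at 1.5. Both tests hold their level.

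**Step 4: the other significance level.** At two-sided 0.05 with 24 months per patient, the figures are 49.3% → 52.6% at HR per SD 1.35, 46.4% → 52.8% at 1.5, and 36.9% → 50.5% at 2.0. At 0.05 the design needs 191 events for 80% power, more than the 130 patients planned. Adjustment cannot close that gap.

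**The case against.** The strongest reply is that nothing here is wrong. A log-rank test is a valid and standard primary test in a randomised phase II trial, the stated power reproduces, and covariates are often left to an analysis plan, which is not shown. That stands: this is a choice of method that could be improved, not an error.

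Four stronger readings are tempting, and the document does not support them.

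- *The plan fixes an unadjusted log-rank test.* The test appears only in the power sentence. All that can be said is that no other comparative test is named for this endpoint.
- *Baseline activity is recorded for every randomised patient.* The run-in is described as a check that the patient can wear and handle the device. Storage of its values as a baseline variable is a fair inference but is not stated. Step targets based on earlier averages are prescribed only in the intervention arm, so they do not show that an average is computed for controls.
- *Available power is thrown away.* That holds only if activity is prognostic. A double-digit loss appears only at the strongest setting, 2.0 per SD, which nothing in the document supports. Restricting entry to performance status 0 to 2 without care needs may narrow the functional range.
- *The simulated gain is the gain of the proposed model.* The simulation compares one covariate with none. Performance status is a stratification factor and plausibly overlaps with daily steps. The increment beyond performance status, site and regimen was not computed and is likely to be smaller.

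What survives is an asymmetry: next to nothing is lost if activity is uninformative, and a few points or more are recovered if it is prognostic.

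**Conclusion.** The point holds as a recommended, inexpensive improvement. At two-sided 0.20, the power that may be lost by ignoring baseline activity is about 0 points at HR per SD 1.0, 1 to 4 points at 1.2 to 1.35, 5 to 6 points at 1.5, and 13 to 14 points at 2.0. It is probably less once the randomisation strata are in the model. These figures assume exponential times given the covariate, proportional conditional hazards, a normally distributed covariate entered in its correct form, complete run-in data, and prognostic strengths that are assumed throughout. The log-rank test remains valid. The use of 0.20 for power and 0.05 for declaring significance is a separate and larger problem in the same section.

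**What to change.** Before outcome data are seen, state under Statistical considerations that the primary comparison of disability-free survival is a Cox model with treatment, the randomisation strata, and log mean daily steps as a continuous covariate.

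- Take steps only from run-in days before the randomisation date. The Table 2 footnote places T1 between study entry and chemotherapy, which could fall after allocation, although the Discussion puts the baseline assessment first.
- Confirm that run-in values are stored for both arms.
- Use the strata actually applied at randomisation. The Abstract includes stage, but Statistical considerations does not.
- Keep the log-rank test as a sensitivity analysis. Age may be added, but no calculation here supports it.

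The cost is a sentence or two of statistical wording and a data check, with no new visits or patients. There are two small downsides: the hazard ratio becomes conditional on baseline activity and the strata, and the functional form must be fixed in advance. The two significance levels must be reconciled separately.
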